Both high-intensity and low-to-moderate intensity strength and endurance training during (neo-)adjuvant chemotherapy will reduce the negative treatment effects on muscle fiber CSA, mitochondrial function, cellular stress, and thus reduce the negative effects on cardiorespiratory fitness and muscle function compared to usual care. High-intensity training will be superior to low-to-moderate-intensity training in counteracting the negative treatments effects.Both high-intensity and low-to-moderate intensity strength and endurance training during (neo-)adjuvant chemotherapy will increase the muscle and blood levels of potential antitumor myokines compared to usual care.Treatment including taxane administration will have larger negative effects on muscle fiber CSA, mitochondrial function, cellular stress, and thus cardiorespiratory fitness and muscle function compared to taxane-free treatment, regardless of the training intensity.

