### Study Design

This study is a 2-group randomized controlled trial (Figure 1). The participants will be randomly allocated into 1 of the 2 training groups: one group performing the combination of strength and endurance training with high intensity and the other group performing the training with low-to-moderate intensity during (neo-)adjuvant treatment for breast cancer. To measure the effect of the treatment itself, a parallel usual care group receiving no supervised training will be recruited from another pool of patients. This will be from patients living too far away from the study site to participate in training and from a usual care control group from another substudy within the Phys-Can consortium carried out at Uppsala University Hospital [31]. The usual care group will have the same inclusion and exclusion (see below) criteria as the 2 training groups in this study. Muscle biopsies, questionnaires, and blood samples will be collected from the training groups before the first chemotherapy cure (T0). The first 2-4 weeks after cure 1 will be used as a familiarization period for tests and exercises and for completing the remaining T0 tests. Testing will include measurements of physical capacity, body composition, and physical activity levels. All measurements, including muscle biopsies, questionnaires, and blood samples, will be repeated halfway into the treatment (T1) and after completion of treatment (T2). In the participants in the usual care group, measurements will be performed at T0 and T2 only. Training will start between cure 2 and cure 3 and will last throughout the treatment period, which is approximately 6 months.

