### Randomization

Participants from Haukeland University Hospital will be randomized in a 1:1 ratio into the 2 training groups stratified by treatment (neoadjuvant or adjuvant treatment). The investigator performing the analyses on muscle biopsies will be blinded for this randomization. As described, participation in the usual care group will be from patients living too far away from the study site at Haukeland University Hospital or from Uppsala University Hospital and will not be randomized.

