### Statistical Analyses

Data will be analyzed according to the intention-to-treat principle. Analyses will include standard descriptive statistics, 2-sided *t* tests, correlation, regression, and 2-way repeated-measures analysis of variance or the comparable nonparametric test as necessary to examine the differences between and within groups at T0, T1, and T2. In addition, a per-protocol analysis, that is, adherence to the protocol, will be conducted. Should imbalances in important variables be detected, sensitivity analyses will also be added including these as covariates in the model.

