## Results

This study is funded by Active Against Cancer (Aktiv mot kreft) (May 2013) and the Norwegian Cancer Society (December 2018). It has been registered at ClinicalTrials.gov (identifier NCT05218876). At Haukeland University Hospital, inclusion started in December 2016 and the last participant is expected to be recruited in December 2022. As of June 2022, we enrolled 38 (19 with biopsies) participants to the high-intensity training group, 36 (19 with biopsies) participants to the low-to-moderate intensity training group, and 5 (4 with biopsies) participants to the usual care group. The recruitment to the usual care group from Uppsala University Hospital started in December 2018 and is finished with a total of 12 patients completing all data collection. Data analyses of the patients from Haukeland University Hospital will start in fall 2022. Data analyses of the patients at Uppsala University Hospital started in January 2022 and is ongoing. The first results are expected to be published in spring 2024.

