Although the primary outcome of this study is muscle fiber CSA, we are also including a wide range of biological measurements, including specific proteins involved in skeletal muscle hypertrophy, protein degradation/protein control, and regulators of muscle fiber function. These analyses will provide further insight into the underlying mechanism through which chemotherapy affects muscle tissue and therefore, muscle function, and how training with different training intensities could be used as a therapeutic measure to counteract the side effects of chemotherapy. We will recruit patients undergoing chemotherapy with anthracyclines, taxanes, or a combination of both. Given a large enough number of patients receiving different treatments, this will give us the opportunity to investigate if different chemotherapy regimens affect the adaptations to training at different intensities. Due to individual treatment protocols, there probably will be differences between participants in the treatment regimen, for example, different type and doses of chemotherapy. This might lead to differences between the 2 training groups and between the training groups and the usual care control group in treatment. The lack of randomization to the usual care control group is also a limitation. This will, together with the fact that most participants in this group are treated at a different site than the training groups, further increase the risk of differences between the training groups and the usual care control group in the treatments and other relevant factors. The results from this study are planned to be published in scientific peer review journals and at scientific congresses.

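### For the two non-randomised comparisons, covariate adjustment is only a sensitivity analysis that depends on a detected imbalance, so their main estimates are open to confounding the article itself expects

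*Protocol article*

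**What the plan says.** **Who is randomised.** The Randomization section allocates Haukeland women 1:1 to the two training groups, stratified by neoadjuvant or adjuvant treatment. Under Study Design, "a parallel usual care group receiving no supervised training will be recruited from another pool of patients". These are women living too far away to train, "or from Uppsala University Hospital and will not be randomized".

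**Regimen.** Taxane use is neither allocated by the trial nor a stratification factor. The Discussion states: "Due to individual treatment protocols, there probably will be differences between participants in the treatment regimen".

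**What rests on these contrasts.** The first part of hypothesis 1 and all of hypothesis 2 compare training with usual care. Hypothesis 3 says: "Treatment including taxane administration will have larger negative effects on muscle fiber CSA". The Introduction makes the taxane comparison conditional on enough women receiving each treatment.

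**The analysis rule.** Statistical Analyses applies intention-to-treat and lists t tests, correlation, regression and repeated-measures ANOVA. It names no covariates and does not match methods to comparisons. It then adds: "Should imbalances in important variables be detected, sensitivity analyses will also be added including these as covariates in the model".

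**What the article expects.** The Discussion says that the lack of randomisation to usual care, together with the different site, will "further increase the risk of differences between the training groups and the usual care control group in the treatments and other relevant factors".

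**The concern.** The Discussion predicts that the usual care group will differ from the training groups, but the analysis rule does not act on the prediction. A wait-and-see approach to covariates is defensible where randomisation makes imbalance a matter of chance. It is hard to defend where the groups differ by distance from the site, hospital, country or the oncologist's choice of regimen. In those contrasts adjustment is part of estimating the effect at all, and it should not depend on whether an imbalance happens to be noticed in a small group. Intention-to-treat adds nothing either, since the trial assigned neither usual care nor taxane.

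At stake are the claims that training counteracts the effects of chemotherapy on muscle and that taxane regimens do more harm. As the rule stands, the main estimate behind each would be unadjusted.

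**Working it through.** **Inputs from the article (Results, Abstract).** Enrolled by June 2022: 38 high intensity (19 with biopsies), 36 low-to-moderate (19 with biopsies), 17 usual care (16 with biopsies). Of the usual care women, 5 (4 with biopsies) are from Haukeland and 12 from Uppsala.

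**The plan's own figures.** The article gives no number for imbalance or confounding. Its only related figures are the sample sizes: 10 per group for 80% power and 16 for 95%. With a two-sample t test, two-sided 5% (alpha is not stated), n = 10 at 80% implies a standardised effect of 1.325. At that effect, 95% power needs 15.8, so 16 per group, and power at 16 is 95.2%. The figures agree with each other and are not in dispute.

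**Site separation.**
- All usual care women: 12 / 17 = 0.71.
- With biopsies: (16 − 4) / 16 = 12 / 16 = 0.75.
- Trained women from Uppsala: none, because only Haukeland women are randomised to training.

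**Would a detection rule notice an imbalance?** The article does not say how imbalance is detected. Assume a two-sided 5% t test on one baseline covariate. The power (noncentral t) is:

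| True imbalance | 19 v 16 (one training group, biopsied) | 38 v 16 (both training groups, biopsied) |
|---|---|---|
| 0.3 SD | 14% | 17% |
| 0.5 SD | 30% | 38% |
| 0.8 SD | 63% | 75% |

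**What would an unadjusted estimate carry?** Bias in outcome SDs = imbalance (SD) × correlation of the covariate with the outcome as analysed. Both inputs are assumed.
- Lowest: 0.3 × 0.3 = 0.09 SD.
- Middle: 0.5 × 0.5 = 0.25 SD.
- Highest: 0.8 × 0.5 = 0.40 SD.

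If training had no effect, a nominal 5% unadjusted test with these biases would reject about 6% to 21% of the time (19 v 16) or 6% to 26% (38 v 16).

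**Scale.** Against the implied design effect, 0.09 / 1.325 = 7% and 0.40 / 1.325 = 30%. A bias of this order would not by itself create an effect as large as the one the sample size implies, but it could distort a smaller one.

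The article gives no counts by taxane use, so no such illustration is possible for that contrast.

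**The case against.** **The main aim is randomised.** A reader might infer that the trial's headline result is confounded. The documents do not support this: the Discussion names high versus low-to-moderate intensity as the main aim, and that contrast is randomised and stratified. This objection stands in full and confines the point to the other two contrasts.

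**The Uppsala figure.** The Results say that recruitment there "is finished with a total of 12 patients completing all data collection", and a reader might infer that the group was selected for having finished. The article does not show this. The Abstract's enrolled total of 17 is 5 + 12, and nothing says that more than 12 enrolled at Uppsala or that anyone was left out. Only a request for clarification remains.

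**Detection need not mean a significance test.** Inspection or standardised differences would fit the wording equally well, so it cannot be said that the trigger would usually fail. Even under the assumed test, it fires more often than not at 0.8 SD.

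**Repeated-measures ANOVA removes stable differences in level.** This is correct for the group-by-time term. The correlation assumed above must therefore be with change when change is what is compared. Covariates such as regimen, age and stage could plausibly relate to change, so the exposure is narrowed but not removed.

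**Regression is listed, the limitation is admitted, and details belong in an analysis plan.** Regression is tied to no comparison or covariate. The admission changes no analysis. A missing covariate list would indeed be no finding in an article. The problem is the stated rule, which makes adjustment secondary and conditional.

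**Conclusion.** The point holds for training versus usual care (hypothesis 1, first part, and hypothesis 2) and, if it is carried out, for taxane versus taxane-free treatment (hypothesis 3). Their main estimates are open to confounding that the article anticipates for usual care and that follows from clinician-chosen regimens for taxane. They are not shown to be confounded, and neither the direction nor the size can be derived from the article.

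The site figure, 12 of 17 (71%), is a fact of the design. The bias range and detection probabilities are illustrations that rest on the assumed imbalances, correlations and 5% test. The rule should be changed, but the randomised intensity comparison is not affected.

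**What to change.** For these two contrasts only:

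1. Make a prespecified covariate-adjusted model the main analysis, delete the imbalance trigger, and keep the unadjusted result as the sensitivity analysis.
2. Use a short list from data already collected (Study Design, Background Variables): T0 value of the outcome, age, stage, and neoadjuvant or adjuvant treatment. Add taxane use for training versus usual care. Add training group for taxane versus taxane-free. Regimen must not be a covariate in the latter, because taxane use defines the exposure.
3. Limit intention-to-treat and causal wording to high versus low-to-moderate intensity. Report the other contrasts as observational, with residual site confounding. Adjustment cannot remove the latter, since only 5 usual care women (4 with biopsies) share the training site.
4. State whether the 12 Uppsala women are all who enrolled there, and include any others with data.

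**Cost.** With one training group against usual care, 19 + 16 = 35 biopsied women leave 33 residual degrees of freedom unadjusted. Five covariates, with stage I to III taking two terms, use 6 more and leave 27. That is affordable, but with about 16 biopsied usual care women the list should not grow. Claims about usual care and taxane become more cautious. The Results section placed the Haukeland analyses in the future (fall 2022), so at that point the list could be fixed before the comparison was seen. If those analyses have since begun, the date on which the list was fixed should be reported.

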## Results

This study is funded by Active Against Cancer (Aktiv mot kreft) (May 2013) and the Norwegian Cancer Society (December 2018). It has been registered at ClinicalTrials.gov (identifier NCT05218876). At Haukeland University Hospital, inclusion started in December 2016 and the last participant is expected to be recruited in December 2022. As of June 2022, we enrolled 38 (19 with biopsies) participants to the high-intensity training group, 36 (19 with biopsies) participants to the low-to-moderate intensity training group, and 5 (4 with biopsies) participants to the usual care group. The recruitment to the usual care group from Uppsala University Hospital started in December 2018 and is finished with a total of 12 patients completing all data collection. Data analyses of the patients from Haukeland University Hospital will start in fall 2022. Data analyses of the patients at Uppsala University Hospital started in January 2022 and is ongoing. The first results are expected to be published in spring 2024.

## Discussion

The main aim of this study is to compare the effects of a high-intensity strength and endurance training program with those of a low-to-moderate intensity strength and endurance training program on muscle cellular outcomes, muscle function, and cardiorespiratory fitness in women undergoing breast cancer chemotherapy. These results will also be compared with those of the group treated with usual care to investigate how (neo-)adjuvant treatment with chemotherapy will affect these variables and how high and low-to-moderate intensity trainings can counteract the effects of treatment. We hypothesize that the usual care control group will experience negative treatment effects on muscle fiber CSA and mitochondrial function, leading to reduced muscle function and cardiorespiratory fitness. We further expect that both high-intensity training and low-to-moderate intensity training performed by the training groups will counteract the negative treatment effects and that high-intensity training will be superior to low-to-moderate-intensity training. The results of our study are expected to provide insights on how regular exercise during treatment may counteract the side effects of chemotherapy on physical functioning and muscle tissue and how training intensity impacts these effects. Such knowledge can be used to design effective physical exercise programs, helping an increasing number of individuals with breast cancer during and following chemotherapy and possibly reducing the long-lasting side effects and ultimately improve the quality of life.

Forty women recently diagnosed with breast cancer, with 20 in each group, will give us a larger study population than those in previous studies on muscle cellular outcomes [12,41,42] to draw conclusions from. Furthermore, to our knowledge, this will be the first randomized controlled study comparing the effectiveness between high-intensity strength and endurance training and low-to-moderate intensity strength and endurance training during (neo-)adjuvant treatment on muscle cellular outcomes in patients with breast cancer. We are also recruiting participants who are not willing to undergo muscle biopsies, giving us an even larger study population when analyzing the other outcomes. As high-intensity training is shown to induce larger improvements in maximal oxygen uptake and muscle strength in both healthy individuals and in various patient populations [27,28], it should also be more effective in patients with breast cancer during chemotherapy. However, it is not known to which extent chemotherapy interferes with normal adaptation to physical training, and the high-intensity training is severely more challenging. Consequently, high-intensity training may be less feasible during chemotherapy, and lower adherence to the planned training in some periods of treatment may reduce training effectiveness. However, the feasibility of the current high-intensity training program has been confirmed in the large-scale Phys-Can study [29], in which ~75% of the participants completed the 6-month training program.

Although the primary outcome of this study is muscle fiber CSA, we are also including a wide range of biological measurements, including specific proteins involved in skeletal muscle hypertrophy, protein degradation/protein control, and regulators of muscle fiber function. These analyses will provide further insight into the underlying mechanism through which chemotherapy affects muscle tissue and therefore, muscle function, and how training with different training intensities could be used as a therapeutic measure to counteract the side effects of chemotherapy. We will recruit patients undergoing chemotherapy with anthracyclines, taxanes, or a combination of both. Given a large enough number of patients receiving different treatments, this will give us the opportunity to investigate if different chemotherapy regimens affect the adaptations to training at different intensities. Due to individual treatment protocols, there probably will be differences between participants in the treatment regimen, for example, different type and doses of chemotherapy. This might lead to differences between the 2 training groups and between the training groups and the usual care control group in treatment. The lack of randomization to the usual care control group is also a limitation. This will, together with the fact that most participants in this group are treated at a different site than the training groups, further increase the risk of differences between the training groups and the usual care control group in the treatments and other relevant factors. The results from this study are planned to be published in scientific peer review journals and at scientific congresses.

In summary, previous research underlines the positive potential of regular physical exercise during cancer treatment on outcomes such as physical function, mental health, fatigue, and quality of life in women with breast cancer [10,43,44]. However, research on the specific cellular effects of training with different intensities has not been performed. This study will provide important information on the effects of a high-intensity training versus low-to-moderate intensity strength and endurance training programs on skeletal muscle cellular outcomes, muscle function, and cardiorespiratory fitness in women diagnosed with breast cancer undergoing chemotherapy. It will also give important information about the cellular mechanisms through which chemotherapy may reduce physical performance and how training with different intensities may counteract these side effects. This knowledge can be used to design training programs that are both effective and feasible for patients with breast cancer during treatment to counteract the side effects of chemotherapy and ultimately increase the daily function and quality of life.

## Appendix

Multimedia Appendix 1 Peer review report by: Norwegian Cancer Society (Oslo, Norway).

## Abbreviations

CSA: cross-sectional area
Hsp: heat shock protein
IL: interleukin
Phys-Can: Physical Training and Cancer
RM: repetition maximum
T0: test period before the first chemotherapy cure
T1: test period halfway into the treatment
T2: test period after completion of treatment
TNF: tumor necrosis factor
VO_2max_: maximal oxygen uptake
